#### **4.2.10. Exclusion Criteria (Genetic Cohort- PD Subjects)**

- 4.2.10.1. A clinical diagnosis of dementia as determined by the investigator (Appendix 1).
- 4.2.10.2. Subjects participating in VMAT-2 PET imaging have received any of the following medications that might interfere with F-AV-133 PET imaging: neuroleptics, metoclopramide, alpha methyldopa, methylphenidate, reserpine, or amphetamine derivative, within 2 weeks prior to the Screening F-AV-133 injection.
- 4.2.10.3. Current treatment with anticoagulants (e.g., coumadin, heparin) that might preclude safe completion of the lumbar puncture.
- 4.2.10.4. Condition that precludes the safe performance of routine lumbar puncture, such as prohibitive lumbar spinal disease, bleeding diathesis, or clinically significant coagulopathy or thrombocytopenia.
- 4.2.10.5. Any other medical or psychiatric condition or lab abnormality, which in the opinion of the investigator might preclude participation.
- 4.2.10.6. Previously obtained MRI scan with evidence of clinically significant neurological disorder (in the opinion of the Investigator).

#### **4.2.11. Inclusion Criteria (Genetic Cohort- Unaffected Subjects)**

- 4.2.11.1. Male or female age 45 years or older at baseline with a LRRK2 or GBA mutation and/or a first degree relative with a LRRK2 or GBA mutation

**OR**

- 4.2.11.2. Male or female age 30 years or older at baseline with a SNCA mutation and/or a first degree relative with a SNCA mutation
- 4.2.11.3. Willingness to undergo genetic testing
  - unaffected subjects at high risk of LRRK2, GBA or SNCA mutation due to first degree relative with a LRRK2, GBA or SNCA mutation may choose either to be informed of the results or remain unaware of the results
  - unaffected subjects from an ethnic or geographic group known to have relatively high risk of LRRK2, GBA or SNCA mutation (such as people of Ashkenazi Jewish or Basques descent) **and** who have a family member (either alive or deceased) who has/had PD must be willing to be informed of their own testing results
- 4.2.11.4. Ability to provide written informed consent in accordance with Good Clinical Practice (GCP), International Conference on Harmonization (ICH), and local regulations.
- 4.2.11.5. Willing and able to comply with scheduled visits, required study procedures and laboratory tests.
- 4.2.11.6. For subjects taking any of the following drugs (Neuroleptics, metoclopramide, alpha methyl dopa, methylphenidate, reserpine, or amphetamine derivative) must be willing and medically able to hold the medication for at least 5 half-lives before DaTSCAN™ imaging.
- 4.2.11.7. Women who are pregnant or lactating will not undergo DaTSCAN™ and/or F-AV-133 imaging assessments. (The imaging assessments that would have occurred during this time will be waived)
  - Includes a negative urine (or serum if required by site) pregnancy **test on day of Screening scan prior to injection (DaTSCAN™ and/or F-AV-133).**
  - Includes a negative serum pregnancy test prior to Screening scan injection (F-AV-133 only).
- 4.2.11.8 Women participating in VMAT-2 PET imaging must be of non-childbearing potential **or** be using a highly effective method of birth control 14 days prior to until at least 24 hours after injection of F-AV-133).
  - Highly effective method of birth control is defined as practicing at least one of the following: A birth control method that results in a less than 1% per year failure rate when used consistently and correctly, such as oral contraceptives for at least 3 months prior to injection, an intrauterine device (IUD) for at least 2 months prior to injection, or barrier methods, e.g., diaphragm or combination condom and spermicide. Periodic abstinence (e.g. calendar, ovulation, symptothermal, post-ovulation methods) is not acceptable.
  - Non-child bearing potential is defined as a female that must be either postmenopausal (no menses for at least 12 months prior to Screening) or surgically sterile (bilateral tubal ligation, bilateral oophorectomy or hysterectomy).

#### **4.2.12. Exclusion Criteria (Genetic Cohort- Unaffected Subjects)**

- 4.2.12.1. A clinical diagnosis of PD
- 4.2.12.2. A clinical diagnosis of dementia as determined by the investigator (Appendix 1).
- 4.2.12.3. GDS score greater than or equal to 10 (GDS score of 5 – 9 requires Investigator discretion to enter study).
- 4.2.12.4. STAI Form Y-1 greater than or equal to 54 requires Investigator discretion to enter study.
- 4.2.12.5. Subjects participating in VMAT-2 PET imaging have received any of the following medications that might interfere with F-AV-133 PET imaging: neuroleptics, metoclopramide, alpha methyl dopa, methylphenidate, reserpine, or amphetamine derivative, within 2 weeks prior to the Screening F-AV-133 injection.
- 4.2.12.6. Current treatment with anticoagulants (e.g., coumadin, heparin) that might preclude safe completion of the lumbar puncture.
- 4.2.12.7. Condition that precludes the safe performance of routine lumbar puncture, such as prohibitive lumbar spinal disease, bleeding diathesis, or clinically significant coagulopathy or thrombocytopenia.
- 4.2.12.8. Any other medical or psychiatric condition or lab abnormality, which in the opinion of the investigator might preclude participation.
- 4.2.12.9. Previously obtained MRI scan with evidence of clinically significant neurological disorder (in the opinion of the Investigator).

Note: New enrollments of LRRK2 or GBA mutation carriers into the Genetic Registry are being ceased with amendment 12. Subjects who are not eligible for enrollment into the Genetic Cohort will not be eligible for participation in PPMI.

#### **4.2.13. Inclusion Criteria (Genetic Registry)**

- 4.2.13.1. Male or female age 18 years or older.
- 4.2.13.2. Individual with a SNCA mutation or with a first degree relative having a SNCA mutation
- 4.2.13.3. Willingness to undergo genetic testing, but may choose either to be informed of the results or remain unaware of the results
- 4.2.13.4. Ability to provide written informed consent in accordance with Good Clinical Practice (GCP), International Conference on Harmonization (ICH), and local regulations.
- 4.2.13.5. Willing and able to comply with scheduled visits, required study procedures and laboratory tests.

#### **4.2.14 Exclusion Criteria (Genetic Registry)**

- 4.2.14.1 A clinical diagnosis of dementia as determined by the investigator (Appendix 1).
- 4.2.14.2. Any other medical or psychiatric condition or lab abnormality, which in the opinion of the investigator might preclude participation.

- 4.2.14.3. Previously obtained MRI scan with evidence of clinically significant neurological disorder (in the opinion of the Investigator).

### **4.3 Age and Gender Matching**

Enrollments will be monitored centrally by the Steering Committee with the goal of achieving age and gender balance across the PD and Healthy Control subjects. Individual sites should generally attempt to match healthy control subjects as closely as possible in age (target within 5 years) and gender to the PD subjects enrolled at the site. Sites will be instructed if recruitment restrictions need to be implemented as the study progresses in order to maintain a balanced population.

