asymmetric, putamen>caudate loss of dopaminergic uptake and the imaging loss correlates with worsening clinical symptoms in cross-sectional evaluation. In addition, DAT ligands demonstrate reductions in activity with normal aging.

In longitudinal studies of PD progression, F-Dopa, VMAT2, DAT ( $\beta$ -CIT and CFT), using both PET and SPECT have demonstrated an annualized striatal rate of reduction of about 4% to 13% in PD patients compared with 0% to 2.5% change in healthy controls. Evidence from studies of hemi-PD subjects provides further insight into the rate of progression of disease. In early hemi-PD there is a reduction in F-Dopa, VMAT2 and DAT of about 50% in the effected putamen and of 25-35% in the unaffected putamen. Since most patients will progress clinically from unilateral to bilateral in 3-6 years it is therefore likely that the loss of these in vivo imaging markers of dopaminergic degeneration in the previously unaffected putamen will progress at about 4-10% per annum.

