An additional cohort of Prodromal subjects will be included in the clinical, imaging and biologic assessments of PPMI. Approximately 100 Prodromal subjects will be enrolled and followed over a 5-10 year period. Prodromal subjects with RBD, and/or hyposmia with DAT binding ranging from no DAT deficit to moderate DAT deficit will be selected (most subjects with DAT binding <80% of age expected striatal DAT binding based on the existing PPMI healthy subject database). Since we are uncertain about the exact distribution of DAT binding in this group, and while we anticipate that the majority of subjects (approx. 80) will have a range of DAT deficit similar to subjects with early PD, we will also select no DAT deficit or minimal DAT deficit subjects (approx. 20) to be similar in age, gender, and risk profile to those with mild to moderate DAT deficit. Subjects will not be informed of their DAT binding. It is anticipated that approximately 400 screening SPECT scans will be completed in order to identify the 100 Prodromal subjects for participation and enrollment.

An additional cohort of subjects selected because of genetic risk will be included in the clinical, imaging and biologic assessments of PPMI. Approximately 1200 subjects will be enrolled and followed over a 5-10 year period. Approximately 600 of these 1200 subjects will be evaluated as part of the Genetic Cohort and approximately an additional 600 will be evaluated as part of the Genetic Registry. The Genetic Cohort participants will be evaluated similarly to the already enrolled PPMI PD and healthy control cohort. The Genetic Registry participants will be evaluated at less frequent intervals to augment and broaden the follow-up of PD subjects and family members with PD associated mutations and are in addition to the Genetic Cohort.

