## **4.2. Selection of Study Population**

### **4.2.1. Inclusion Criteria (Parkinson Disease Subjects)**

- 4.2.1.1. Patients must have at least two of the following: resting tremor, bradykinesia, rigidity (must have either resting tremor or bradykinesia); OR either asymmetric resting tremor or asymmetric bradykinesia.
- 4.2.1.2. A diagnosis of Parkinson disease for 2 years or less at Screening.
- 4.2.1.3. Hoehn and Yahr stage I or II at Baseline.
- 4.2.1.4. Not expected to require PD medication within at least 6 months from Baseline.
- 4.2.1.5. Male or female age 30 years or older at time of PD diagnosis.
- 4.2.1.6. Confirmation from imaging core that screening dopamine transporter SPECT scan is consistent with dopamine transporter deficit (or for sites where DaTSCANTM is not available that VMAT-2 PET scan is consistent with VMAT deficit).
- 4.2.1.7. Ability to provide written informed consent in accordance with Good Clinical Practice (GCP), International Conference on Harmonization (ICH), and local regulations.
- 4.2.1.8. Willing and able to comply with scheduled visits, required study procedures and laboratory tests.
- 4.2.1.9. Women may not be pregnant, lactating or planning pregnancy during the course of the study.

- Includes a negative urine pregnancy test on day of Screening scan prior to injection (DaTSCANTM and/or F-AV-133).
  - Includes a negative serum pregnancy test prior to Screening scan injection (F-AV-133 only).
- 4.2.1.10. Women participating in VMAT-2 PET imaging must be of non-childbearing potential **or** be using a highly effective method of birth control 14 days prior to until at least 24 hours after injection of F-AV-133).
- Non-child bearing potential is defined as a female that must be either postmenopausal (no menses for at least 12 months prior to Screening) or surgically sterile (bilateral tubal ligation, bilateral oophorectomy or hysterectomy).

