#### **4.2.3. Inclusion Criteria (Healthy Control Subjects)**

- 4.2.3.1. Male or female age 30 years or older at Screening.
- 4.2.3.2. Ability to provide written informed consent in accordance with Good Clinical Practice (GCP), International Conference on Harmonization (ICH), and local regulations.
- 4.2.3.3. Willing and able to comply with scheduled visits, required study procedures and laboratory tests.
- 4.2.3.4. Women may not be pregnant, lactating or planning pregnancy during the course of the study.
  - Includes a negative urine pregnancy test on day of Screening scan prior to injection (DaTSCANTM and/or F-AV-133).
  - Includes a negative serum pregnancy test prior to Screening scan injection (F-AV-133 only).
- 4.2.3.5. Women participating in VMAT-2 PET imaging must be of non-childbearing potential **or** be using a highly effective method of birth control 14 days prior to until at least 24 hours after injection of F-AV-133).
  - Non-child bearing potential is defined as a female that must be either postmenopausal (no menses for at least 12 months prior to Screening) or surgically sterile (bilateral tubal ligation, bilateral oophorectomy or hysterectomy).
  - Highly effective method of birth control is defined as practicing at least one of the following: A birth control method that results in a less than 1% per year failure rate when used consistently and correctly, such as oral contraceptives for at least 3 months prior to injection, an intrauterine device (IUD) for at least 2 months prior to injection, or barrier methods, e.g., diaphragm or combination condom and spermicide. Periodic abstinence (e.g. calendar, ovulation, symptothermal, post-ovulation methods) is not acceptable.

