#### **4.2.7. Inclusion Criteria (Prodromal Subjects)**

- 4.2.7.1. Subjects must have at least one of the following characteristics:
  - Hyposmia:*
    - a) Male or female age 60 years or older
    - b) Confirmation from olfactory core that olfaction as determined by UPSIT is at or below the 10th percentile by age and gender
  - REM Behavior Disorder (RBD):*

- a) Male or female age 60 years or older
  - b) Confirmation from sleep core that subject's Polysomnography (PSG) meets criteria for RBD and/or clinical diagnosis of RBD by site investigator including existing PSG.
- 4.2.7.2. Confirmation from imaging core that screening dopamine transporter SPECT scan (or V-MAT-2 PET scan for sites where DaTSCAN™ is not available) is read as eligible (see below)
- About 80 subjects will have a range of DAT deficit similar to subjects with early PD (mild to moderate DAT deficit). About 20 subjects will be selected with no DAT deficit or minimal DAT deficit similar in age, gender, and risk profile to those with mild to moderate DAT deficit.
- 4.2.7.3. Ability to provide written informed consent in accordance with Good Clinical Practice (GCP), International Conference on Harmonization (ICH), and local regulations.
- 4.2.7.4. Willing and able to comply with scheduled visits, required study procedures and laboratory tests.
- 4.2.7.5. Women may not be pregnant, lactating or planning pregnancy during the course of the study.
- Includes a negative urine pregnancy test on day of screening scan prior to injection (DaTSCAN™).
  - Includes a negative serum pregnancy test prior to Screening scan injection (F-AV-133 only).
- 4.2.7.6. Women participating in VMAT-2 PET imaging must be of non-childbearing potential **or** be using a highly effective method of birth control 14 days prior to until at least 24 hours after injection of F-AV-133).
- Non-child bearing potential is defined as a female that must be either postmenopausal (no menses for at least 12 months prior to Screening) or surgically sterile (bilateral tubal ligation, bilateral oophorectomy or hysterectomy).

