### 14.4. Planned Analyses

Information summarizing planned analyses is described below. Further details regarding the analyses and plans for additional analyses will be contained in the PPMI Data Analysis Plan.

- 14.4.1. **Comparison of baseline characteristics among various subsets.** The first set of analyses will involve a comparison of baseline characteristics among the various subsets enrolled into the study. Continuous variables will be examined using a t-test and dichotomous variables will be examined using a chi-square test. Appropriate assumptions will be assessed for each comparison and any necessary adjustments (i.e., transformations) will be made prior to analysis. All analyses will be conducted at the 0.05 level.
- 14.4.2. **Comparison of short-term change in progression endpoints.** The second set of analyses will examine the short-term change during the first six months

for each progression endpoint. For continuous progression endpoints, the change over time will be modeled using a mixed model approach. For dichotomous progression endpoints, a logistic regression model will be fit. For each 'full' model of interest, an initial model will consist of all baseline characteristics, an indicator variable for whether the subject is a PD patient or healthy control, and all possible two-way interactions. We will utilize backwards selection to build a model for each progression endpoint.

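### Prodromal subjects enter at 60 or older, while controls and PD subjects enter from 30 and are age-balanced only to each other, so unadjusted comparisons of Prodromal levels can reflect age

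*Protocol*

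**What the plan says.** **Entry ages.** Both routes into the Prodromal cohort (hyposmia and RBD, section 4.2.7) carry the same floor: "Male or female age 60 years or older". For controls, section 4.2.3 has "Male or female age 30 years or older at Screening". For PD subjects, section 4.2.1 has "Male or female age 30 years or older at time of PD diagnosis". SWEDD subjects inherit the PD criteria (4.2.5).

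**Balancing.** Section 4.3 sets central monitoring "with the goal of achieving age and gender balance across the PD and Healthy Control subjects" and asks sites to "match healthy control subjects as closely as possible in age (target within 5 years) and gender to the PD subjects enrolled at the site". The only age similarity stated for Prodromal subjects is internal to that cohort: about 20 with no or minimal deficit are to be "similar in age, gender, and risk profile to those with mild to moderate DAT deficit" (4.1).

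**Comparisons.** PD versus Prodromal appears in the primary objective (14.2) and in the secondary objectives (14.3). Section 14.5 adds exploratory comparisons of Prodromal subjects with PD, control and SWEDD subjects.

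**Methods.** For baseline characteristics across cohorts, 14.4.1 states: "Continuous variables will be examined using a t-test and dichotomous variables will be examined using a chi-square test". For short-term change, 14.4.2 starts a mixed or logistic model from all baseline characteristics plus a PD-or-control indicator, then applies backward selection. Section 14.4.4 extends these analyses to PD subsets and does not name the Prodromal cohort. Further detail is left to a Data Analysis Plan that is not shown.

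**Age as a factor.** The background (1.1) says "DAT ligands demonstrate reductions in activity with normal aging".

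**The concern.** An entry floor 30 years higher, with no matching across cohorts, will tend to make the Prodromal cohort older than its comparators unless nearly all comparators happen to be 60 or older. The controls are assembled to resemble PD subjects, not Prodromal subjects. DAT binding falls with age on the protocol's own account, and cognitive, autonomic and CSF measures can be expected to vary with age as well.

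The one stated test that reaches Prodromal versus control or PD is unadjusted. The one stated multivariable model neither contains a Prodromal term nor guarantees that age is retained. A difference in level caused by age could then be read as a prodromal marker, which is the kind of result this study exists to produce.

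**Working it through.** **1. The protocol's own figure.** Section 14.5 gives a detectable standardised difference of 0.24 for 400 PD versus 200 controls (two-sided 0.05, power 0.80). From d = (1.960 + 0.842) × √(1/n₁ + 1/n₂):
- 200 vs 400: 2.802 × 0.0866 = 0.243 (stated 0.24).
- 150 vs 300: 2.802 × 0.100 = 0.280 (stated 0.28).

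The table is reproduced. It has no entry for a Prodromal comparison of means. The same formula for 100 Prodromal versus 200 controls gives 2.802 × 0.1225 = 0.34.

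**2. Inputs for the age effect.** From the protocol: floors of 60 and 30, about 100 Prodromal, 200 controls, 400 PD. Assumed, because the protocol gives no ages:
- Comparator ages are normal with mean 55, 60 or 65 and SD 8 to 12, truncated to 30–90.
- Prodromal ages follow the same distribution truncated to 60–90.
- The correlation r between age and the outcome is 0.1 to 0.5.
- There is no disease effect.

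**3. Formulas.** Age-only difference in SD units: b = r × (gap in mean age) / (SD of age). Standard error: √(1/100 + 1/n). Rejection rate of a two-sided 5% test: Φ(b/SE − 1.96) + Φ(−b/SE − 1.96).

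**4. Central case** (mean 60, SD 10, which becomes about 9.9 after truncation; gap 7.9 years; SE for 100 vs 200 = 0.1225):

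| r | b | rejects, vs 200 controls | rejects, vs 400 PD |
|---|---|---|---|
| 0.1 | 0.1 × 7.9/9.9 = 0.08 | 10% | 11% |
| 0.2 | 0.16 | 26% | 30% |
| 0.3 | 0.24 | 50% | 58% |
| 0.5 | 0.40 | 91% | 95% |

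At r = 0.3 the age-only difference equals the smallest detectable difference in the protocol's own table.

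**5. Whole grid** (SD 8 to 12, r 0.1 to 0.5, 100 vs 200):

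| Comparator mean age | Gap (years) | b (SD) | Rejects |
|---|---|---|---|
| 55 | 9.8–12.3 | 0.11–0.62 | 15% to about 100% |
| 60 | 6.4–9.3 | 0.08–0.40 | 10–91% |
| 65 | 3.6–6.5 | 0.04–0.29 | 7–65% |

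The answer depends strongly on how old the comparators turn out to be. With a comparator mean of 65 and r = 0.1, the excess over 5% is slight.

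**The case against.** **No test is stated for the primary Prodromal contrast.** A reader might infer that PD versus Prodromal in the primary objective will be tested without adjustment. The protocol does not say so. That objective, like 2.2.5, concerns change over time. The t-test and chi-square test appear only under baseline comparisons. The change model starts from all baseline characteristics, which would ordinarily include age. Covariates for Prodromal rates of change may properly sit in the Data Analysis Plan, so their absence is no error. This stands, and the point is confined to levels.

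**The calculation does not describe change.** A constant offset in level cancels in a change score. For DAT, a Prodromal-versus-control comparison of change cannot be made at all, because controls are scanned at Screening only (control schedule; 6.3.1). This stands too.

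**The age gap is inferred.** A reader might take it as established that the Prodromal cohort is older by a known amount, or might multiply an assumed gap by the 0% to 2.5% annual change quoted for healthy controls in 1.1. The protocol reports no age distributions, and that range pools F-Dopa, VMAT2 and DAT tracers from longitudinal studies. Only a range under stated assumptions is supportable.

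**The floor of 60 does not define every Prodromal group.** Objective 2.2.5 and section 14.1 pool in the Unaffected Genetic Cohort, whose floors are 45, or 30 for SNCA. The gap for the pooled group is unknown. That group is, however, also outside the balancing in 4.3.

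**Age is partly handled at entry.** DAT selection refers to age-expected binding, hyposmia is a percentile by age and gender, and the 20 subjects with no or minimal deficit resemble the other 80 in age. None of this adjusts later comparisons of raw values with controls or PD subjects.

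**The 14.5 comparisons are labelled exploratory.** True, but that does not justify a method that leaves a known confounder in place when the remedy is free.

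**Conclusion.** The point holds for comparisons of level. The floors of 60 and 30, the balancing confined to PD and controls, the unadjusted baseline tests, and a selection step that can remove age are all in the text. Together they allow a baseline Prodromal difference to be produced by age.

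Its size cannot be computed from the protocol. Under the assumptions above it is about 0.04 to 0.62 SD, with false rejection in about 10% to 91% of central-case comparisons of 100 versus 200. The result rests on the assumed comparator ages, the assumed correlations, and Prodromal ages following the upper part of the comparator distribution. It does not extend to rates of change. The matter deserves correction mainly because the stated method is open to the bias and the remedy needs no new data.

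**What to change.** In 14.4.1 and 14.4.2, state that every comparison of the Prodromal cohort (and of the Unaffected Genetic Cohort where it is pooled with it) with control, PD or SWEDD subjects uses a model that always contains age and sex, both exempt from backward selection. For 14.4.1 this replaces the plain t-test or chi-square test in those comparisons.

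Add a sensitivity analysis of the 60-and-older Prodromal cohort against comparators aged 60 or older. It guards against leaning on an assumed age relationship fitted largely in subjects under 60. Section 4.3 needs no change, since it already names only PD and controls.

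Demographics are already collected at Screening, so the main analysis costs wording only. The restricted analysis loses precision. Under the assumed age distributions, 27% to 73% of the 200 controls (54 to 146) would be 60 or older. The detectable difference against 100 Prodromal subjects is then 2.802 × √(1/100 + 1/54) = 0.47 to 2.802 × √(1/100 + 1/146) = 0.36 SD, compared with 0.34 SD using all 200. If the Data Analysis Plan already retains age and sex, one cross-referencing sentence in 14.4 is enough for the main analysis.
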